### Statistical analysis

2.12

Data will be analyzed blind to treatment group according to the intention-to-treat principle by an independent biostatistician. Continuous variables will be presented as mean (SD) and nominal variables tabulated as absolute and/or relative frequencies. Comparisons between binary outcomes will be performed using Fisher exact test. Continuous variables will be compared using the unpaired *t* test and Mann-Whitney *U* test as indicated. Comparisons of BP and NIHSS scores between the 2 groups at different time-points will be analyzed using repeated-measures analysis of variance for the overall effect. Finally, the relative changes in BP, CBF, and NIHSS scores at 1, 24, and 72 hours after the initiation of treatment, and 90-day outcomes, will be compared using analysis of covariance. Baseline BP and use of antihypertensive medications before admission will be used as covariates in analyses of BP differences. Baseline NIHSS will be used as a covariate in analyses of stroke severity. Statistical significance is set at the 5% level. There would be no interim analysis (Table 3).

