**Methods::**

In a randomized controlled trial, 54 thrombolysed AIS patients with a systolic BP of 160 to 180 mm Hg will be randomized to early intensive BP lowering (systolic target range 140–160 mm Hg) or guideline-based BP management (systolic range 160–180 mm Hg) during first 72-hours using primarily intravenous labetalol. We hypothesize that early intensive BP lowering will not reduce CBF by 20% and/or increase the volume of hypoperfused tissue by >20% on computed tomographic perfusion. Clinical outcome will be assessed using a dichotomized modified Rankin scale (scores 0–1 as excellent outcome vs scores 2–6 as dead or dependent) at 90 days. Other outcome would be symptomatic intracerebral hemorrhage. The trial is registered at ClinicalTrials.gov, NCT03443596.

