## Introduction and rationale

1

Elevated systolic blood pressure (BP), defined as >140 mm Hg, is commonly observed in patients with acute ischemic stroke (AIS).^[1]^ Potential mechanisms and associations include pre-existing hypertension,^[1]^ activation of neuroendocrine systems,^[2]^ stress of hospitalization,^[3]^ location of the infarct,^[4]^ stroke subtype,^[5]^ severity,^[6]^ and a homeostatic response to raised intracranial pressure.^[7]^ Whether treatment of this acute hypertensive response improves clinical outcome is unknown.^[7,8]^ Arguments in favor of treatment include the strong positive relationship between degree of elevation in BP and death or dependency,^[9]^ cerebral edema,^[10]^ early and late stroke recurrence,^[11,12]^ and extrapolation of potential benefits in acute intracerebral hemorrhage (ICH).^[13–15]^ Arguments against treatment center on the natural tendency for BP to normalize within a few days of presentation,^[1,5,6]^ and potential harms associated with altered cerebral perfusion related to dysfunction of autoregulation.^[7,16,17]^ Some studies suggest that adverse outcomes are associate with early antihypertensive therapy.^[18,19]^

The primary aim of the study is to determine the effect of early intensive BP lowering (systolic BP target 140–160 mm Hg) initiated within 6 hours of symptom onset and maintained for 72 hours in AIS patients treated with intravenous tissue plasminogen activator (IV-tPA) on cerebral blood flow (CBF), measured with computed tomographic (CT) perfusion imaging. We hypothesize that this treatment approach is safe and that such magnitude of BP lowering does not reduce CBF by 20% and/or increase the volume of hypoperfused tissue by >20% on CT perfusion or adversely affect functional outcomes at 90 days. Secondary aims are to obtain preliminary estimates of the clinical impact of early intensive BP lowering on functional outcomes and symptomatic intracerebral hemorrhage (sICH).

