### Sample size calculations

2.11

Allowing for within-subject and between-subjects variation, a sample size of 27 patients per group was estimated to allow detection of a difference of 20% [15% standard deviation (SD)] in relative change in CBF and/or the volume of hypoperfused tissue between the early intensive BP lowering and control groups, with 90% power and significance set at 5% (α = 0.050, 2-tailed). The sample size was increased to 30 patients per group to allow for treatment dropouts, crossovers, and potential loss to follow-up.

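### Fisher's exact test for the binary secondary outcomes is valid but conservative at 27 to 30 patients per arm; Boschloo's test plus a risk difference with its interval would be a cheap improvement.

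*Protocol article*

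**What the plan says.** Section 2.12 (Statistical analysis) of the protocol article fixes the test: "Comparisons between binary outcomes will be performed using Fisher exact test". The same section sets the threshold: "Statistical significance is set at the 5% level". Section 2.7 (Outcomes) lists two binary outcomes, both secondary: an mRS score of 2 to 6 at day 90, and sICH by the SITS-MOST definition.

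The Introduction gives their purpose: "Secondary aims are to obtain preliminary estimates of the clinical impact of early intensive BP lowering on functional outcomes and symptomatic intracerebral hemorrhage". It also puts forward the hypothesis that intensive lowering is safe and does not worsen function at 90 days.

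Section 2.11 claims power for the perfusion measures only. It says "a sample size of 27 patients per group was estimated" and then "The sample size was increased to 30 patients per group". The abstract implies 27 per arm: "54 thrombolysed AIS patients with a systolic BP of 160 to 180 mm Hg will be randomized". No event rate and no power are given for either binary outcome.

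**The concern.** Fisher's test conditions on the total number of events. In small samples few tables are then possible, so the probability of rejecting under no difference falls well below the nominal level. The unused error is lost power. The loss matters more than usual here because the hypothesis is that the intervention does no harm, so a test that rejects too seldom errs in the hoped-for direction. A p-value just above 0.05 for bleeding could be taken as reassurance. A p-value also does not provide the estimate that the secondary aim asks for.

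**Working it through.** **Inputs from the document.** Fisher's test and the 5% level (section 2.12); 27 to 30 patients per arm (section 2.11 and abstract); 1:1 allocation by minimization (section 2.3), which does not guarantee exactly equal arms. The event rates used for power are assumptions.

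**The plan's own figures.** There is none for the binary outcomes. The perfusion calculation (a 20% difference, SD 15%, 90% power, two-sided 5%) gives 2 × (1.960 + 1.282)² × 15² / 20² = 11.8, so 12 per arm (13 with the t distribution), not 27. That is a separate matter; arms of 27 to 30 are taken here as given.

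**1. Attained size of Fisher's test.** For every 2×2 table, reject if the two-sided p ≤ 0.05. Sum the binomial probabilities of the rejected tables at a common event rate, then take the maximum over that rate.

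| Arms | Maximum size |
|---|---|
| 27 v 27 | 2.63% |
| 28 v 28 | 2.77% |
| 29 v 29 | 2.51% |
| 30 v 30 | 2.74% |
| 27 v 28 | 3.77% |
| 28 v 29 | 3.43% |
| 29 v 30 | 3.64% |
| 27 v 30 | 3.59% |

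For rare events the size is far smaller: at a common rate of 5% it is 0.10% (27 per arm) and 0.15% (30 per arm).

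**2. Five sICH against none.** Given five events in all, the probability that all fall in an arm of size n, out of N patients, is C(n,5)/C(N,5).

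- *27 v 27:* C(27,5)/C(54,5) = 80,730/3,162,510 = 0.0255. The opposite extreme is equally likely, so p = 2 × 0.0255 = 0.051. At 30 v 30, p = 0.052.
- *27 v 28, events in the smaller arm:* 80,730/3,478,761 = 0.0232. The opposite extreme has probability 98,280/3,478,761 = 0.0283. It is more likely than the observed table, so it is not counted, and p = 0.023.
- *27 v 28, events in the larger arm:* both extremes count, and p = 0.0283 + 0.0232 = 0.051 (0.0515 before rounding).

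One patient's difference in arm size can therefore change the verdict. Six against none is significant with equal arms (p = 0.023-0.024).

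**3. Boschloo's test.** It uses Fisher's p-value as the test statistic and calibrates it over all tables with the arm totals fixed. Its rejection region has a maximum size of 4.46% (27 per arm) and 4.69% (30 per arm). For five against none, p = 0.026 and 0.027; in the unequal arms tried, p was below 0.04 whichever arm had the events.

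**4. Power (assumed rates, exact binomial sums).**

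| Arms | Rates | Fisher | Boschloo |
|---|---|---|---|
| 27 v 27 | 40% v 70% | 48.1% | 57.8% |
| 27 v 27 | 50% v 75% | 37.3% | 44.9% |
| 27 v 27 | 5% v 25% | 36.1% | 50.0% |
| 27 v 28 | 40% v 70% | 55.1% | 59.5% |
| 27 v 28 | 5% v 25% | 39.6% | 49.7% |
| 27 v 27 | 5% v 10% | 1.3% | 3.9% |

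In the 27 v 28 rows the higher rate is in the arm of 28. The gain varies with the rates and the imbalance and is small in some unequal-arm settings.

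**5. What an interval would show.** For 5/27 v 0/27 the difference is 18.5 points. The Wilson limits are 8.2% to 36.7% and 0% to 12.5%. Newcombe's lower limit is 0.185 − √[(0.185 − 0.082)² + 0.125²] = 0.023. The upper limit is 0.185 + (0.367 − 0.185) = 0.367. The 95% interval is 2.3 to 36.7 points.

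**The case against.** Fisher's test is a standard, valid choice for sparse tables, and preferring another exact test is a choice between two valid methods. That stands, and it sets the weight of this point.

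A reader might infer three stronger things.

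- *That the plan misstates its error rate.* Section 2.12 sets a threshold. It does not promise an attained error of 5%, and Fisher's test cannot exceed that threshold.
- *That five bleeds against none would always be reported as non-significant, or that 2.7% is a ceiling.* Both fail beyond exactly equal arms of 27 or 30, and minimization with dropout makes slight imbalance plausible. Five against none is also the zero-cell table nearest the boundary.
- *That the plan will treat a non-significant result as safety.* The article nowhere says so. Section 2.8 gives safety monitoring to an independent board that reviews batches of 10 patients.

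It is also fair to say that section 2.12 tabulates frequencies, so the rates in each arm will be visible, and that it mentions analysis of covariance for 90-day outcomes. The choice of interval method is commonly left to an analysis plan, so its absence here is not a fault. Finally, sample size is the main limit: at 5% v 10% both tests have almost no power.

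What remains is that this article itself names the test, and that a valid alternative did better in every configuration checked.

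**Conclusion.** This is a worthwhile, inexpensive improvement, not the correction of an error. With 27 equal arms and the assumed rates, the gain is 7.6 points (44.9 − 37.3) to 13.9 points (50.0 − 36.1) for the larger differences. At 27 v 28 it is 4.4 points (59.5 − 55.1) and 10.1 points (49.7 − 39.6). For a small sICH difference the gain has no practical value.

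The size results rest only on the arm sizes and the 5% threshold. The power results rest on event rates that the article does not supply. Both outcomes are secondary with no power claimed, so no stated conclusion depends on the change. The interval is the more useful half of the remedy, because it answers the estimation aim and shows how much harm the data leave open.

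**What to change.** In section 2.12, replace the sentence on binary outcomes with one stating that day-90 mRS 2-6 and sICH will be compared by Boschloo's unconditional exact test (two-sided, 5%, arm totals fixed). Add that each will be reported as a risk difference with a 95% confidence interval by one named method, Newcombe or Miettinen-Nurminen, as the main secondary result. State that a non-significant difference will not be read as evidence of safety.

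The arm totals should be named as the fixed margin because software output depends on it: at 27 per arm, five against none gives 0.026 with the arms fixed, but 0.021 if the table is entered the other way round.

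The cost is a sentence or two, with no extra patients or data. The downsides are that Boschloo's test is less familiar to readers than Fisher's, and that its p-value and the chosen interval may disagree in borderline cases.

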### Background care

2.5

All patients will be managed in a high-dependency stroke unit with repeated neurological examination using the NIHSS, noninvasive BP, and heart rate monitoring (consistent recordings using automatic devices, every 15 minutes for 1 hour, then hourly for 23 hours, then 6 hourly until discharge). All BP measurements are obtained from the nonparetic arm. Rescue endovascular intervention (before inclusion into the study and randomization) is allowed according to local institutional practice. Figure 1 describes the workflow in the study.

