### Data collection and follow-up

2.6

All patients undergo repeat CT-perfusion scans at 24 and 72 hours postrandomization, to obtain the estimates of the effects of BP on various cerebral perfusion parameters. NIHSS scores are assessed daily until day 7 (or hospital discharge, if earlier) (Table 2). Patients are followed-up at day 90, where the NIHSS and mRS scores are reassessed. These assessments are conducted in-person by trained staff who are blind to the treatment allocation.

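### Repeated-measures ANOVA fits poorly with NIHSS and BP series that end at discharge, and may drop early-discharged or deceased patients if the daily series is used

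*Protocol article*

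**What the plan says.** Section 2.12 names the method for the serial measurements: "Comparisons of BP and NIHSS scores between the 2 groups at different time-points will be analyzed using repeated-measures analysis of variance". It does not say which time points enter that model. The next analysis it describes is a separate analysis of covariance of "relative changes in BP, CBF, and NIHSS scores at 1, 24, and 72 hours after the initiation of treatment, and 90-day outcomes". The section adds that "Baseline NIHSS will be used as a covariate in analyses of stroke severity", and sets the analysis principle: "Data will be analyzed blind to treatment group according to the intention-to-treat principle by an independent biostatistician".

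The collection schedule is given elsewhere. Section 2.6: "NIHSS scores are assessed daily until day 7 (or hospital discharge, if earlier"). The same section also says: "Patients are followed-up at day 90, where the NIHSS and mRS scores are reassessed". Section 2.5 has BP taken every 15 minutes for an hour, then hourly to 24 hours, "then 6 hourly until discharge".

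Section 2.7 makes CT perfusion the primary outcome, with day-90 mRS and symptomatic intracerebral haemorrhage as the secondary outcomes. Serial NIHSS is not a listed outcome.

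**The concern.** Conventional repeated-measures ANOVA needs a value at every time point for every patient and discards patients with a gap. Here the gaps are built into the schedule: a patient discharged on day 4 has no NIHSS for days 5 to 7, and a patient who dies has none afterwards.

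Both events come after randomisation and can be affected by treatment. Discharge plausibly follows recovery, which is what NIHSS measures. The patients left with a full series would no longer be a randomised comparison, and omitting the others sits badly with intention-to-treat.

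The trial's hypothesis (Introduction) is that intensive lowering is safe. A blurred between-arm NIHSS difference would matter for that claim, and with 27 to 30 patients per group (section 2.11) there is little precision to spare.

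**Working it through.** **Plan's own figure.** None exists for this analysis. The article gives no NIHSS standard deviation, expected NIHSS difference or discharge rate. Every simulation input below is therefore an assumption, and the results show what can happen, not what will.

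**Step 1: schedule against method.** NIHSS runs daily to day 7 or discharge, so series length differs between patients. A daily day 1–7 ANOVA would be unbalanced by design. Adding day 90 does not restore the missing in-hospital days, and deaths and losses before day 90 would create further gaps.

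**Step 2: direction of bias.** Assumed model for days d = 1 to 7:

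Y = b + s·d + g·e·min(d/3, 1) + error

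Baseline b has mean 10 and SD 5. Slope s has mean −0.4 and SD 0.4. Error SD is 1.5, and g is 0 or 1 for arm. Effect e is −2 for all, or −3 and −1 split at baseline 10. There are 400,000 patients per scenario and no deaths.

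True average effect: −2 × (1/3 + 2/3 + 5)/7 = −1.71.

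Discharge can occur on each of days 3 to 6 with probability h:

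- unrelated to NIHSS: logit h = −1.6, so h = 0.168 and the complete fraction is (1 − 0.168)⁴ = 0.479
- baseline-driven: logit h = −1.6 − 0.3(b − 10)
- current-NIHSS-driven: logit h = −1.6 − 0.3(Y − 8)

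Complete-series estimates, with the baseline-adjusted estimate in brackets:

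| Effect pattern | Full data | Unrelated | Baseline-driven | Current-NIHSS-driven |
|---|---|---|---|---|
| Constant | −1.75 | −1.76 (−1.72) | −1.74 (−1.72) | −0.87 (−1.57) |
| Larger in severe | −1.69 | −1.70 (−1.72) | −2.22 (−2.23) | −1.55 (−1.96) |
| Larger in mild | −1.72 | −1.71 (−1.71) | −1.21 (−1.22) | −0.05 (−0.97) |

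Between 40% and 48% of patients had a complete series. Reversing the sign (+2, harm) gave the same pattern: for a constant effect with current-NIHSS discharge, 1.69 became 0.93, or 1.59 adjusted.

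A second simulation used a single mechanism: harm of 2 points, median baseline 9, discharge from day 3 with a 30 to 50% daily chance once NIHSS was at or below 4 to 8, and 8% daily mortality at NIHSS 24 or more. A full-data difference of 1.89 to 1.96 fell to between 1.22 and 0.73, reported without baseline adjustment.

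**Step 3: precision.** If a fraction f of patients has a complete series, an effect with 90% power at full size has power Φ((1.960 + 1.282)·√f − 1.960).

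| f | About n of 27 | Power |
|---|---|---|
| 0.9 | 24 | 87% |
| 0.8 | 22 | 83% |
| 0.7 | 19 | 77% |
| 0.5 | 14 | 63% |

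Example for f = 0.8: 3.242 × 0.894 − 1.960 = 0.94, and Φ(0.94) = 0.83.

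**Step 4: if only 1, 24 and 72 hours are used.** Sections 2.4 and 2.6 plan a CT perfusion scan at 72 hours for every patient, so few series should be cut by discharge before then. Both simulations start discharge on day 3, so their bias comes from the later days.

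**The case against.** The article never says that days 1 to 7 enter the ANOVA, that only complete series are used, or that anyone is excluded. Missing-data handling is commonly left to a fuller plan. The NIHSS times that section 2.12 does name are 1, 24 and 72 hours, where little is lost. Serial NIHSS is supportive, has a separate analysis of covariance, and is not the only check on harm: the haemorrhage definition includes NIHSS deterioration, and the safety board reviews every 10 patients.

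Much of this stands, and it rules out several stronger readings that a reader might infer:

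- **NIHSS collection ends altogether at discharge.** It does not; NIHSS is repeated at day 90.
- **The plan restricts the analysis to complete cases, or contradicts intention-to-treat.** That is inferred from how the method usually behaves. No exclusion is written.
- **Group differences are necessarily attenuated.** The table shows no bias, amplification or attenuation according to mechanism. Baseline NIHSS, a covariate the plan already names, recovers most of the loss for a constant effect (−0.87 to −1.57), though less when the effect is larger in mild patients (−0.05 to −0.97).
- **BP is equally affected.** Nothing shows that discharge depends on BP, and the treatment contrast lies within 72 hours.

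What the objection does not remove is the mismatch itself. The point is not a missing rule: the article names both the method and the truncated schedule, and a fuller plan that kept this method for the daily series would inherit the problem. The 1, 24 and 72 hour points belong to the analysis of covariance, and nothing ties the ANOVA to them.

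**Conclusion.** The concern holds conditionally. If the daily in-hospital series is the input, conventional repeated-measures ANOVA would drop randomised patients for a reason arising after randomisation and plausibly linked to recovery. Loss of precision then follows directly: 90% power becomes 83% with 80% of series complete and 63% with 50%.

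Bias in the NIHSS comparison is possible, but its direction is not established. It is plausibly towards no difference if discharge follows current NIHSS, and less so after baseline adjustment. All sizes rest on assumed NIHSS distributions, effects and discharge rates.

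The consequence is limited because this is a supportive analysis. The change is still worth making, since a better-suited method is available without new data.

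**What to change.** In section 2.12, replace repeated-measures ANOVA for BP and NIHSS with a mixed model for repeated measures. Suggested content:

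- fixed effects for arm, time, arm-by-time and the baseline value of the measure
- the time points that enter each model, stated in advance
- all randomised patients contribute every available measurement, with no exclusion for an incomplete series
- a sensitivity analysis that gives patients who die the worst NIHSS score from death onwards, because the mixed model otherwise treats values after death as merely unobserved

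**Cost.** Analysis wording only, with standard software and no new data or visits. The model relies on data being missing at random. That is reasonable when discharge depends on NIHSS values already recorded, but the data cannot prove it.

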### Randomization and blinding

2.3

All study subjects undergo CT perfusion to obtain the baseline cerebral hemodynamic parameters. Participating patients are randomly assigned to early intensive BP lowering (140–160 mm Hg) or the guideline-based management (160–180 mm Hg) in a 1:1 ratio using a central computer generated sequence with minimization according to age (<60 vs ≥60 years), severity (NIHSS score <10 vs >10), and baseline systolic B (<150 vs >150 mm Hg). The treating physician is unblinded to the treatment assignment as he/she is required to titrate BP control with IV labetalol. However, all 90-day outcome assessments are conducted by physicians who are kept blind to the treatment allocation.

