### Intervention

2.4

Patients allocated to early intensive BP lowering are to receive IV labetalol according to a predefined protocol (Table 2), whereas those assigned guideline-based BP management receive current standard of care. All study participants are closely monitored and a CT perfusion scan is repeated at 24 and 72 hours postrandomization. The treatment regime is an initial IV bolus (5–10 mg each, repeated at 10-minute intervals, maximum dose 80 mg) followed by continuous IV infusion to maintain the desired BP.

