### Outcomes

2.7

The primary outcome is the assessment of CT perfusion studies and evaluate whether CBF in the affected region reduces by >20% and/or the volume of hypoperfused tissue increases by >20% if BP is treated intensively during the first 72 hours in thrombolysed AIS patents. Secondary endpoint is dependency at day-90, defined by scores 2 to 6 on the mRS. Secondary outcome would be sICH, defined by the Safe Implementation of Thrombolysis in Stroke-Monitoring Study (SITS-MOST) criteria as large local or remote parenchymal ICH (type 2) combined with a neurological deterioration (≥4 points on the NIHSS) from baseline or death within 36 hours.^[20]^ Data are entered prospectively on to case report forms without any personal identifiers.

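### The ANCOVA sentence gives CBF no baseline covariate, leaves out hypoperfused volume, lists CBF at an hour when no scan is done, and uses a different clock from the scans

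*Protocol article*

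**What the plan says.** **Outcome.** Under Outcomes (2.7), the primary aim is to "evaluate whether CBF in the affected region reduces by >20% and/or the volume of hypoperfused tissue increases by >20" per cent. There are therefore two perfusion measures.

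**Analysis.** Statistical analysis (2.12) applies analysis of covariance to "the relative changes in BP, CBF, and NIHSS scores at 1, 24, and 72 hours after the initiation of treatment", and adds that "90-day outcomes, will be compared using analysis of covariance". Covariates are then assigned outcome by outcome:
- BP: "Baseline BP and use of antihypertensive medications before admission will be used as covariates in analyses of BP differences".
- Severity: "Baseline NIHSS will be used as a covariate in analyses of stroke severity".
- CBF: none named.
- Hypoperfused volume: not mentioned in the sentence.

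**Scans.** Randomization and blinding (2.3) gives every subject a baseline perfusion scan. Under Intervention (2.4), "a CT perfusion scan is repeated at 24 and 72 hours postrandomization", and Data collection and follow-up (2.6) repeats this. CT perfusion image analysis (2.10) counts three time points.

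**Allocation.** Section 2.3 uses "minimization according to age (<60 vs ≥60 years), severity (NIHSS score <10 vs >10), and baseline systolic B (<150 vs >150 mm Hg").

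**The concern.** The article fixes covariates for two supporting outcomes and stops short of the primary one. Read literally, the CBF comparison is an analysis of covariance without a covariate, which is an unadjusted comparison of relative change. Forming a relative change divides by the baseline value, but it does not remove the dependence on that value: patients with a high baseline tend to show a larger fall. The best available predictor of follow-up flow is collected in everyone and goes unused.

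The minimization factors are missing from the CBF analysis too. Age is a covariate nowhere; NIHSS and BP serve only for other outcomes. When allocation forces balance on prognostic factors and the model ignores them, the standard error is too large and the test too cautious. The article hopes to show that flow is not reduced, so lost precision matters here: a real reduction becomes easier to miss.

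Two points of wording compound this. The sentence lists a CBF value that the scan schedule cannot supply. And it starts the clock at treatment initiation, while the scans start it at randomization.

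**Working it through.** **1. The plan's own figure.** Sample size calculations (2.11) gives 27 per group for a 20% difference, SD 15%, 90% power, two-sided 5%. As written, n = 2 × 15² × (1.96 + 1.282)² / 20² = 11.8, so 12 per group (13 by the t test), not 27. An SD of about 22.7% would give 27. The present point does not depend on this, but both SDs are used in step 4.

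**2. Variance with and without the baseline.** The documents give no baseline-to-follow-up correlation ρ, so 0.3 to 0.7 is an assumed range. With equal variances σ² at the two times:
- change score: 2σ²(1 − ρ)
- baseline-adjusted: σ²(1 − ρ²)
- ratio: (1 − ρ²) / [2(1 − ρ)] = (1 + ρ)/2

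| ρ | Ratio, difference or log-change | Ratio, percentage change (simulated, log-SD 0.3 assumed) |
|---|---|---|
| 0.3 | 0.65 | about 0.70 |
| 0.5 | 0.75 | 0.78 |
| 0.7 | 0.85 | 0.86 |

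The formula is exact for a difference or log-change score only. For percentage change, the measure that the article uses, the gain is a little smaller: about 14–30% less variance instead of 15–35%.

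**3. Dependence on baseline.** For a difference or log-change score the correlation of change with baseline is −√[(1 − ρ)/2] = −0.59, −0.50 and −0.39. For percentage change under the same assumed log-SD it is about −0.54, −0.47 and −0.37.

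**4. What this means for power at 27 per group.** Standard error = SD × √(2/27); power = Φ(20/SE − 1.96).
- SD 15%: SE 4.08, power 99.8% unadjusted, so little is left to gain.
- SD 22.7%: SE 6.17, power 90.0% unadjusted. Multiplying SE by √0.65, √0.75 and √0.85 gives 4.97, 5.34 and 5.69, and power of 98.0%, 96.3% and 94.0%.

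**5. Leaving out the minimization factors.** Suppose they explain a share R² of outcome variance (assumed) and minimization balances them fully (also assumed). The true size of a nominal 5% test is then 2[1 − Φ(1.96/√(1 − R²))]: R² of 0.10, 0.20 and 0.30 give 3.9%, 2.8% and 1.9%. Only age and NIHSS can contribute. The systolic cut lies at 150 mm Hg and patients enter at 160–180 mm Hg (2.1), so all eligible patients fall on the same side of it.

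**6. Times, side by side.**

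| Item | Statistical analysis (2.12) | Scan schedule (2.3, 2.4, 2.6, 2.10) |
|---|---|---|
| CBF times | 1, 24, 72 h | baseline, 24, 72 h |
| Clock starts at | initiation of treatment | randomization |

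No scan exists at 1 hour. BP is recorded every 15 minutes in the first hour (2.5), so a 1-hour BP does exist.

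**The case against.** This is a condensed article, and a full covariate list normally sits in the analysis plan, which is not shown. An analysis of covariance has a covariate by definition, so it is an inference from silence that CBF has none. That is fair as far as it goes. But the article does not defer the matter: it assigns covariates by outcome and passes over the primary one. Naming them is a concrete improvement at no cost.

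The section also never says which test is primary. Hypoperfused volume could fall under its general rules for continuous or binary variables. That stands: the volume is absent from the ANCOVA sentence, not from the whole analysis.

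At the stated SD of 15%, power is already 99.8% without adjustment. That also stands; the gain matters if the true SD is nearer the 22.7% that 27 per group implies.

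Several stronger readings are tempting and not supported:
- *The unadjusted estimate is biased.* Chance baseline imbalance shifts the estimate in a given trial; with 27 per group a typical imbalance is √(2/27) = 0.27 SD. Over randomizations the shift averages to zero.
- *The SD of percentage change must exceed 15%.* An assumed log-SD of 0.3 gives 24–39%, but 0.15 with ρ = 0.7 gives about 12%. The article cannot settle it.
- *Control patients have no time zero.* Their range equals the entry range and they receive standard care, so some may start no drug. But treatment may mean assigned management, and Tables 2 and 3 are not shown.
- *A 1-hour CBF analysis is truly intended.* The 1-hour point may be meant for BP and NIHSS only. The sentence does not say so.

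**Conclusion.** The concern holds as a matter of efficiency and consistency, not of validity. The ANCOVA sentence leaves CBF without a named covariate and omits hypoperfused volume, though the baseline values are collected in everyone.

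The cost is precision: variance could fall to 0.65–0.85 of the unadjusted value for a difference or log-change score, and to about 0.70–0.86 for percentage change. Both ranges rest on an assumed ρ of 0.3–0.7 and equal variances, and the second also on one assumed log-SD. Leaving out the minimization factors makes the test conservative by an amount that depends on how prognostic age and NIHSS are for perfusion, which the article does not say. The randomized comparison is not biased on average.

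The 1-hour CBF and the two time origins are real inconsistencies of wording. The first changes no result, because no such data will exist. The second matters only if treatment start differs from randomization, or differs between arms.

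**What to change.** In Statistical analysis:
1. Name both CBF and hypoperfused volume, analysed at 24 and 72 hours by analysis of covariance.
2. Adjust each for its own baseline value, age, baseline NIHSS and baseline systolic BP. Enter systolic BP as a continuous variable, because the 150 mm Hg cut does not divide patients who enter at 160–180 mm Hg.
3. Restrict the 1-hour time point to BP and NIHSS.
4. Time all outcomes from randomization in both arms, the one origin certain to exist for every patient.

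The cost is a change of wording, made before the data are unblinded. Baseline perfusion, NIHSS, systolic BP and age are already obtained for the scans, eligibility or minimization, so no extra scan, visit or patient is needed. Earlier endovascular treatment is not in this list: the article permits it (2.5) but does not name it among the data collected (2.2).
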